## Abstract

**Background:**

Diabetes mellitus (DM) is one of the most common noncommunicable diseases. DM has a substantial negative impact on patients’ quality of life, which is measured using a variety of diabetes-specific measures covering multiple aspects of patients’ psychological state, behavior, and treatment satisfaction. A fully digital data collection system, including patient identification, would represent a substantial advance in how these patient-reported outcome (PRO) data are measured. Within the European Union, one way to identify patients without the involvement of health care professionals is to use the unique 2D matrix codes on the packaging of prescription medication—for example, metformin, the recommended initial treatment for patients with type 2 DM (T2DM).

**Objective:**

In the DePRO study we aim to (1) describe the self-care activities of patients with T2DM using metformin-containing medication; (2) describe the self-reported health status (eg, presence of diabetes complications and quality of life) of these patients; (3) describe associations between self-care activities and demographics and disease characteristics; and (4) assess the usability of the my ePRO app.

**Methods:**

DePRO is an observational, multicenter, cross-sectional, digital, patient-driven study conducted in Germany. Patients with a prescription for a metformin-containing medication will be given a postcard by their pharmacist, which will include a download link for the my ePRO app. In total, 12 diabetes-focused pharmacies, selected to represent urban and rural areas, will be recruited. Participants will use their own mobile device (bring your own device) to download the my ePRO app and access the DePRO study, for which they can register using the 2D matrix code on their medication. An electronic informed consent form will be displayed to the patients and only after giving consent will patients be able to complete the study questionnaires. The PRO instruments used in the study are the Summary of Diabetes Self-Care Activities Scale, the Diabetes Treatment Satisfaction Questionnaire, and the 5 level, 5-dimension EuroQol Questionnaire. Patients will also be asked to complete a questionnaire with items addressing demographics, patient characteristics, disease history, complications, and concomitant medications. Data will be transferred to the study database by the app upon completion of each questionnaire. Statistical analyses of primary and secondary endpoints will be exploratory and descriptive.

**Results:**

Enrollment began in June 2020. The estimated study completion date is December 31, 2020, and the planned sample size is 300 patients.

**Conclusions:**

The DePRO study uses completely digital data collection, including authentication of eligible patients and completion of the study questionnaires. Therefore, the design of the DePRO study represents a substantial advance in the evaluation of the digital capturing of PRO data.

**Trial Registration:**

ClinicalTrials.gov NCT04383041; https://clinicaltrials.gov/ct2/show/NCT04383041

**International Registered Report Identifier (IRRID):**

PRR1-10.2196/21727

## Introduction

### Background

Diabetes mellitus (DM) is one of the most common noncommunicable diseases, with a growing global prevalence which is impacting negatively on the sustainability of health care systems [1]. According to the International Diabetes Federation, DM affected 463 million people globally in 2019, a number forecast to grow to 578 million by 2030 [2]. An estimated 8.5% of the adult population in Europe has DM, with national prevalence rates ranging from 2.4% to almost 15% [3]. DM has a high negative impact on society as a result of the severe comorbidities and complications associated with the disease [4]. Several studies have estimated that 90%-95% of all patients with DM are affected by type 2 DM (T2DM) and that the prevalence of T2DM will continue to increase due to population aging [2,5]. The complications of DM affect patients’ quality of life [6,7] and increase the risk of negative events such as emergency department visits, hospitalization, and death, with consequences for health care costs and the sustainability of health care systems [8]. Clinical recommendations refer to diabetes self-care and self-management as key to preventing disease complications and maintaining patients’ health and quality of life over time [9,10].

Assessment of psychosocial functioning and health-related quality of life has gained prominence in the care and treatment of patients with diabetes over the past decade. This has resulted in the development of a variety of diabetes-specific measures covering multiple aspects of patients’ psychological state, behavior, and treatment satisfaction. These include, for example, the Summary of Diabetes Self-Care Activities Scale (SDSCA) and the Diabetes Treatment Satisfaction Questionnaire (DTSQ) [11,12].

It has been estimated that there were 6.9 million patients with T2DM in Germany in 2015 [13]. The recommended initial treatment for patients with T2DM is metformin [14]; in 2018, a total of 606 million daily doses of metformin were prescribed in Germany, corresponding to 160 different medications provided by 25 marketing authorization holders [15].

Within the European Union the Falsified Medicine Directive (Directive 2011/62/EU) defines “the characteristics and technical specifications of the unique identifier of the safety features … that enables the authenticity of medicinal products to be verified and individual packs to be identified” [16]. This 2D matrix code on the outer packaging of medication contains a country code, a product code, a serial number, the expiry date, and the charge of the medication. Once a patient has possession of the package, the 2D matrix code is no longer an identifier only of the medication, but also of the patient as the user of this medication.

### Objectives

In the DePRO study we aim to (1) describe the self-care activities of patients with T2DM using metformin; (2) describe the self-reported health status (eg, presence of diabetes complications and quality of life) of these patients; (3) describe associations between self-care activities and demographics and disease characteristics; and (4) assess the usability of the my ePRO app.

## Methods

### Study Design

DePRO is an observational, multicenter, cross-sectional, digital, patient-driven study conducted in Germany. Patients with a prescription for a metformin-containing medication will be eligible for participation and will be consecutively invited to participate. Patients receiving metformin-containing medication will be given a postcard by their pharmacist, which will include a download link for the my ePRO app. Patients will conduct the entire study without any support from the pharmacist. Participants will use their own mobile device (smartphone or tablet) to download the my ePRO app and will be directed through the app to the DePRO study. For registration and authentication they will use the unique 2D matrix code on their metformin-containing drug package. An electronic informed consent form will be displayed to the patients and only after giving consent will patients be able to complete the study questionnaires. After completing the questionnaires and uploading a picture of the metformin-containing drug package, patients will receive compensation for their time, in the form of a voucher or a donation to charity (Figure 1 and Multimedia Appendix 1). Data will be transferred to the study database by the app upon completion of each questionnaire. The final data analysis for the study will be performed by a contract research organization, Institut [name], Munich, Germany (IDS).

**Figure 1 figure1:**
[figure not shown]
Recruitment and data capturing process with the my ePRO app.
EQ-5D-5L: 5-level, 5-dimension EuroQol Questionnaire; PIIC: patient information and informed consent form; PRO: patient-reported outcome.

### Ethical Considerations

The study protocol has been approved by the Ethics Committee of the Medical Association North Rhine (approval no. 2020084).

### Patients

Adult patients with a valid prescription for a metformin-containing medication will be enrolled in a public pharmacy after the decision for treatment with metformin has been made by their treating physician and informed consent is given by patients. No restrictions on potential eligibility for the DePRO study will be applied.

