### Data Collection and Outcome Measures

The treating physician will have prescribed a metformin-containing medication, but will not contribute to data collection during the study. The patient’s data and answers to the questionnaires will be captured directly by the patient in the relevant sections of the my ePRO app using their own mobile devices.

By scanning the 2D matrix code with the my ePRO app, the patient is linked to a unique central patient identification code, which is only used for study purposes. For the duration of the study and afterward, only the authorized contract research organization personnel at IDS are able to link the patient identification code to the medication package used. For collection of data on concomitant medication use, the app can be used to scan the barcodes on the outer packaging of both prescription and nonprescription drugs. The number of invited, participating and nonparticipating patients—as stated to the inviting pharmacist—and the reasons given for nonacceptance of study participation will be collected by the pharmacist in a recruitment log.

The PRO instruments used in the study are the SDSCA, the DTSQ, and the 5-level, 5‑dimension EuroQol Questionnaire (EQ-5D-5L). The SDSCA is a questionnaire which assesses levels of self-care in adults with diabetes and was developed by Toobert et al [11]. The DTSQ is used to assess patients’ satisfaction with their diabetes treatment [12]. The EQ-5D-5L is a widely used instrument for measuring generic health status using a 5-dimension descriptive system and a visual analog scale [17], both of which are included in the DePRO study.

To complete the clinical picture of each patient the following variables will be collected in a questionnaire (not previously validated) requesting patients’ self-reported age; sex; weight; height; geographic region (first 2 digits of postal code); concomitant medication; education level; family income; time from the diagnosis of T2DM; occurrence of diabetes microvascular complications (diabetic kidney disease, diabetic retinopathy, diabetic neuropathy, and diabetic foot); occurrence of diabetes macrovascular complications (coronary arterial disease and stroke); and glycated hemoglobin (Hb_A1c_; Table 1 and Multimedia Appendices 2 and 3).

**Table 1 table1:** Data captured within DePRO study by origin.

Data captured		Data source	
		Patient	Pharmacist

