**Patient characteristics**			
	Demography (eg, age, sex, geographic region, education level, family income)	X	
	Patient characteristics (eg, height, weight)	X	
	Disease history	X	
	Microvascular complications (diabetic kidney disease, diabetic retinopathy, diabetic neuropathy, and diabetic foot)	X	
	Macrovascular complications (coronary arterial disease, stroke)	X	
	Glycated hemoglobin (Hb_A1c_)	X	
	Concomitant medication (QR^a^ code scan)	X	

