#### Patient Population Size

The DePRO study aims to assess the current self-care activities of patients with T2DM in Germany within a cross-sectional design by testing the feasibility of data collection with the my ePRO app. We will therefore recruit 12 diabetes-focused pharmacies, selected to represent urban and rural areas across Germany, to participate in the DePRO study. Based on a previously conducted feasibility assessment with these pharmacies, the mean number of patients filling a metformin-containing prescription per quarter is approximately 4500. Assuming a variability of ±15% per quarter, 5175 postcards providing the download code for the my ePRO app will be provided to the pharmacies, representing the maximum sample size. Therefore, a planned recruitment time of 3 months, which covers the typical treatment situation of patients with T2DM (at least quarterly visits are necessary to receive a metformin prescription), determines the sample size of the DePRO study. For sample size considerations, we assume that 7%-10% of invited patients will complete the study. We further assume that the SD of SDSCA would be 13 points, according to the SD observed in the study by Ausili et al [18]. Given this assumption, a sample size of 300 patients is required to obtain a 95% confidence interval of the mean level of self-care with a precision (ie, width of the interval) equal to 3 points.

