## Results

The DePRO study uses completely digital data collection. All data are patient reported and are not verified by any health care professional. The recruitment of patients is not based on the diagnosis of an investigator, but on the consequence of a diagnosis—namely the prescription of an approved drug. By providing software (my ePRO app) to patients and authenticating with available hardware (the outer packaging of the medication, containing the 2D matrix code), it will be possible to collect data directly from patients.

Enrollment began in June 2020. The estimated study completion date is December 31, 2020.

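### Objectives 1 to 3 and the sample size concern metformin-treated T2DM, but entry is open to any adult prescribed metformin and no stated criterion confirms T2DM, even by self-report

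*Protocol article*

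**What the plan says.** **Target population.** Objective 1 in the protocol article (Objectives) is to "describe the self-care activities of patients with T2DM using metformin". Objective 2 refers back to the same patients, and objective 3 relates those self-care activities to demographic and disease characteristics. The Patient Population Size section says the study "aims to assess the current self-care activities of patients with T2DM in Germany". The sixth limitation in the Discussion (Rationale for Study Design) again names metformin-treated T2DM as the population of interest. Objective 4, to "assess the usability of the my ePRO app", is not tied to T2DM.

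**Entry rule.** The Patients section says: "Adult patients with a valid prescription for a metformin-containing medication will be enrolled in a public pharmacy". It then adds: "No restrictions on potential eligibility for the DePRO study will be applied". T2DM is not a criterion there or under Study Design.

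**Diagnosis information.** The Results section explains: "The recruitment of patients is not based on the diagnosis of an investigator". The prescription stands in for the diagnosis. The self-report questionnaire includes "time from the diagnosis of T2DM" (Data Collection and Outcome Measures), and Table 1 lists "Disease history" as reported by the patient. The questionnaire itself is in appendices that are not shown.

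**The concern.** The entry rule is wider than the population that objectives 1 to 3 and the sample size describe, and the article states no step that closes the gap. The safeguards listed in the Discussion are a check for duplicate codes, blocking of the scanner once documentation has started, and a bar on re-entry after withdrawal of consent. They protect against inappropriate or repeated participation, and none concerns diagnosis.

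The SDSCA is described as a measure of self-care in adults with diabetes, and the DTSQ as a measure of satisfaction with diabetes treatment. For someone who takes metformin without having diabetes, neither score measures what it is meant to. For someone with another type of diabetes, the scores may be meaningful but do not belong under a T2DM label. The quantity behind the sample size is a mean, so such answers would go straight into it, and a larger sample would not remove the resulting bias.

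**Working it through.** **1. The two populations side by side**

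| Source in the protocol article | Population |
|---|---|
| Objectives 1 to 3; Patient Population Size; Discussion, sixth limitation | T2DM (treated with metformin) |
| Study Design; Patients | Any adult with a metformin prescription, no restrictions |
| Stated criterion linking the two | None |

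The Background calls metformin the recommended initial treatment for T2DM. Nowhere does the article say that only patients with T2DM receive it.

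**2. The plan's own figure**

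Inputs from Patient Population Size: SD 13, 95% confidence, full interval width 3.

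- n = (2 × 1.96 × 13 / 3)² = 288.6, so 289. With the t quantile, n = 291.
- Width at n = 300: 2 × 1.96 × 13 / √300 = 2.94 (2.95 with t).

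The stated 300 is therefore the calculated number rounded up.

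**3. Precision if the analysis is limited to T2DM**

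Let p be the share of completers without T2DM. The documents give no value, so p is an assumption. SD is held at 13.

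- T2DM patients among 300 completers = 300 × (1 − p)
- Width = 2 × 1.96 × 13 / √(T2DM patients)
- Completers needed to keep 289 with T2DM = 289 / (1 − p), rounded up

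| p (assumed) | T2DM among 300 | Width | Completers needed |
|---|---|---|---|
| 1% | 297 | 2.96 | 292 |
| 5% | 285 | 3.02 | 305 |
| 10% | 270 | 3.10 | 322 |
| 15% | 255 | 3.19 | 340 |

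The expected yield is above 300. The article assumes that 7% to 10% of invited patients complete:

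- of 5175 postcards: 0.07 × 5175 = 362 to 0.10 × 5175 = 518
- of 4500 patients per quarter: 0.07 × 4500 = 315 to 0.10 × 4500 = 450

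With 362 completers and p = 15%, 0.85 × 362 = 308 remain, which is above 291. With 315 completers and p = 15%, 268 remain and the width is about 3.11.

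**4. Bias of the mean if everyone is kept**

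Let d be the difference in mean score between participants without and with T2DM (also an assumption).

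- Mean of the mixture = T2DM mean + p × d, so the shift is p × d.
- Low: 0.05 × 5 = 0.25 points
- Middle: 0.10 × 10 = 1.0 point
- High: 0.15 × 15 = 2.25 points

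The planned half-width is 3 / 2 = 1.5 points. The shift reaches 1.5 only when p × d does, for example at 15% with 10 points or 10% with 15 points.

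**The case against.** The strongest reply is that the design is deliberate and largely disclosed. Authenticating patients by the medicine pack rather than through a clinician is the innovation being tested. The Discussion lists the missing validated diagnosis as a limitation and says that weighing this way of capturing data is part of the study's purpose. This explains why no clinician confirms T2DM. It does not explain why the participant's own report is not used, in a study whose questionnaire data are all self-reported, and it does not bring the eligibility text into line with the objectives.

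The other objections limit how far the point can be taken, and they stand:

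- A reader might infer that no diagnosis information is collected. The article does not support that: T2DM duration and disease history are listed, and the questionnaire, which is not shown, may contain a diabetes-type question or a filter.
- A reader might infer that every objective is affected. App usability (objective 4) is not.
- A reader might infer that all participants will certainly be averaged into the T2DM results. The article defines no analysis sets, and a rule may exist in the full protocol or SAP. What can be criticised is the stated eligibility, which is wider than the stated target.
- No figure in the documents anchors p or d, and the article does not discuss metformin use outside T2DM.

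**Conclusion.** The point holds as a mismatch between the stated population and the stated entry rule. As written, people without T2DM can enter and contribute to SDSCA and DTSQ results presented as T2DM, and no stated criterion uses the self-reported items to prevent this. Disclosing that the diagnosis is not validated does not resolve it.

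The size of the bias is unknown. The 0.25 to 2.25 point range rests wholly on assumed shares and differences and exceeds the planned half-width only towards its upper end, so it does not show that the main result will be materially wrong. Nor do the documents support a claim that the sample size fails. The 300 reproduces, the loss of precision is about 0.1 point at 10%, and the article's own completion assumption gives more than 300 completers.

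The issue is whom the mean describes. It should be corrected before results are labelled as T2DM, but it is a moderate point in a descriptive study and does not undermine the design.

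**What to change.** - Make self-reported T2DM the criterion for the primary analysis set for objectives 1 to 3, using the diagnosis items already collected or one added item on diabetes type.
- Treat a missing diagnosis duration as unknown status, not as absence of T2DM. Patients may skip the item or not recall the date, and dropping them would introduce a new selection. Include them in a sensitivity analysis.
- Report the number and characteristics of those excluded.
- Show the result for all metformin users as secondary, and keep all participants for objective 4.
- If this cannot be done, restate the population and conclusions as adults prescribed metformin.

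**Cost.** The change needs a short analysis-set definition and at most one app item. A few completers leave the primary set and the interval widens slightly (3.10 instead of 3 if 270 remain). Enrolment began in June 2020, so an added item would cover only later participants. The Discussion says that patients cannot be contacted about incomplete data, so earlier participants would have to be classified from the existing items.

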### Study Device: my ePRO App

The my ePRO app is a data capture tool which can be used for either stand-alone studies or piggy-backed on randomized controlled trials and observational studies to track patients’ health status. The app uses standardized, validated patient-reported outcome (PRO) instruments. Furthermore, the app has the capacity to gather additional data (physical activity, face and voice recognition, weather data) based on the research questions in each study. Users are provided with a unique app account, free of charge. By using the quick response (QR) code scanner built into the app patients can scan either a study-specific QR code provided on a patient information leaflet or the medication-specific 2D matrix code on the outer packaging of their medication. The latter option leads to company-specific pages where studies and the respective consent forms are offered. The my ePRO app is available for the most common device types (smartphones and tablets) running the most widespread mobile operating systems (Android and iOS). The my ePRO app was co-developed by IDS and Bayer, and is hosted by IDS.

### Data Transfer and Processing

Generally, the app will be used online. When not connected to the internet (offline mode), the app stores the entered data so that no data loss occurs. Data are transferred to the database as soon as the device is online again.

### Data Collection and Outcome Measures

The treating physician will have prescribed a metformin-containing medication, but will not contribute to data collection during the study. The patient’s data and answers to the questionnaires will be captured directly by the patient in the relevant sections of the my ePRO app using their own mobile devices.

By scanning the 2D matrix code with the my ePRO app, the patient is linked to a unique central patient identification code, which is only used for study purposes. For the duration of the study and afterward, only the authorized contract research organization personnel at IDS are able to link the patient identification code to the medication package used. For collection of data on concomitant medication use, the app can be used to scan the barcodes on the outer packaging of both prescription and nonprescription drugs. The number of invited, participating and nonparticipating patients—as stated to the inviting pharmacist—and the reasons given for nonacceptance of study participation will be collected by the pharmacist in a recruitment log.

The PRO instruments used in the study are the SDSCA, the DTSQ, and the 5-level, 5‑dimension EuroQol Questionnaire (EQ-5D-5L). The SDSCA is a questionnaire which assesses levels of self-care in adults with diabetes and was developed by Toobert et al [11]. The DTSQ is used to assess patients’ satisfaction with their diabetes treatment [12]. The EQ-5D-5L is a widely used instrument for measuring generic health status using a 5-dimension descriptive system and a visual analog scale [17], both of which are included in the DePRO study.

To complete the clinical picture of each patient the following variables will be collected in a questionnaire (not previously validated) requesting patients’ self-reported age; sex; weight; height; geographic region (first 2 digits of postal code); concomitant medication; education level; family income; time from the diagnosis of T2DM; occurrence of diabetes microvascular complications (diabetic kidney disease, diabetic retinopathy, diabetic neuropathy, and diabetic foot); occurrence of diabetes macrovascular complications (coronary arterial disease and stroke); and glycated hemoglobin (Hb_A1c_; Table 1 and Multimedia Appendices 2 and 3).

**Table 1 table1:** Data captured within DePRO study by origin.

Data captured		Data source	
		Patient	Pharmacist
